### Mindfulness-based stress prevention training for medical students (MediMind)

Each meeting begins with various types of mindfulness meditation being practiced and a reflection on the assignments of the last session. The specific contents of the training sessions are described below. With every coping skill we teach our participants, we establish a connection to the idea of mindfulness.

Module I: In the first session, the participants get to know each other and are introduced to the themes ‘mindfulness’ and ‘experiencing stress’. Initially, we use short interaction exercises to connect the participants. Following this, based on actual studies on stress experience and psychological morbidity, the relevance of a stress prevention training for medical students is demonstrated. Subsequently, the participants reflect on their own everyday stressors. Afterwards, the methods of MediMind are presented as effective in dealing with stress experience. This is followed by a brief introduction to the history and mode of action of mindfulness. Using a mindfulness exercise, the principle is experienced and made concrete. A practice assignment allows participants to try different experiments in mindfulness in their daily lives until the next meeting.

Module II: The second module addresses two basic concepts of mindfulness. First, the image of the ‘satellite-position’ as a target state of successful stress management is introduced. It characterizes the ability to observe one’s thoughts, emotions, physical reactions and impulse to act. In exercises and real-life examples, participants learn the importance of a presence-of- mind attitude in order to realize and target stress constructively. In addition, participants learn to address intrusive and distracting thoughts or feelings. Through exercises, the participants learn how an accepting attitude can influence the reduction in these thoughts or feelings and release them. By this approach the dysfunctional effect of displacing or avoiding the experience of stress is made clear. In one assignment, participants are asked to log their own level of stress over the week prior to the next meeting, and practice different experiments to switch into the ‘satellite-position’.

Module III: The manner in which cognitive judgment mechanisms influence one’s own experience is imparted to the participants. For a better understanding, we use a stress induction exercise and study everyday examples in order to derive how one’s own appraisal can have a stress heightening influence. These dysfunctional cognitive judgement mechanisms (errors in reasoning) are discussed by the participants in small groups and then presented to the group. Prior to the next session, an assignment will enable the participants to identify errors in reasoning and practice the use of functional reevaluation. An audio CD with a breathing meditation is handed out to the participants to support the practice of mindfulness meditation.

Module IV: This session deals with personal standards and assumptions that have a causal influence on cognitive judgment mechanisms and thus may exacerbate the experience of stress. With the help of everyday life examples, the idea of ‘stress exacerbating settings’ is conveyed to the participants and they can test themselves to determine their core beliefs. It will then be discussed as to which of these core beliefs exacerbate the experience of stress and which can also be helpful. An educational film that emphasizes some specific assumptions in medical education is used to question them critically. Another focus is to highlight how the stress heightening effect of individual core beliefs can be mitigated. In an exercise participants practice coping with functional stress exacerbating settings in the form of various experiments that are grounded on both mindfulness-based and cognitive behavioral therapy.

Module V: The last module focuses on stress-tolerance skills and the concept of radical acceptance [23]. First, the participants determine the characteristics of individual high-tension situations, from which the necessity for and effectiveness of stress tolerance skills is derived. These are then presented to the group and experienced through exercises. As a last resort, to cope with tense situations that can neither be influenced by their external circumstances nor by stress-tolerance skills, the concept of radical acceptance is developed and applied in a practical exercise. At the end of the training, participants draw conclusions and compile worksheets defining what they learned and what they want to remember in the future.

### Autogenic training

The participants learn basic skills of Autogenic Training according to the Schultz method [54]. This is an auto-suggestive relaxation technique in which participants are first instructed by a qualified coach and subsequently able to instruct themselves. These instructions consist of six exercises with corresponding formulas that are subvocally repeated (e.g. ‘My arm is very heavy’) and suggest specific autonomic sensations: muscular relaxation, vascular dilation, stabilization of heart function, regulation of breathing, regulation of visceral organs and regulation of blood flow in the head [55]. Each session contains a theoretical introduction to the practice, the performance of relaxation techniques and a final discussion. The training will be extended by additional exercises including progressive muscle relaxation, breathing relaxation, exercises for body awareness, imaginary journeys and qigong movements. The participants are provided with information material for individual practice.

### Outcome measures

#### Assessment time points

Measures will be completed by all participants at four assessment time points: (1) baseline, after receiving signed informed consent and before random assignment to the study groups; (2) post-intervention, three weeks after the last training session; (3) follow-up, one year after post-intervention assessment; (4) follow-up, five years after post-intervention assessment. At each assessment time point, participants complete the same questionnaires and standard demographic measures, which take approximately 45 minutes. Additionally, starting with post-intervention, questions relating to stressful life events will be added. The participants will be able to complete the baseline questionnaires after the information lectures or complete an online version. In order to participate in the post-intervention and follow-up assessments, the participants will have the choice of either filling in the questionnaire as a paper-and-pencil version or completing an online version. As an acknowledgment of their participation, 50.- € vouchers will be raffled among the participants. As a special motivation to the participants that have been allocated to the control group, everyone who participated in the questionnaire surveys will receive a 20.- € voucher.

#### Primary outcome measure

*Trier Inventory for the Assessment of Chronic Stress (TICS)* [50]. This measure is used to evaluate different aspects of chronic stress. It consists of 57 items, which participants are asked to answer on a Likert-type scale ranging from 0 (‘I never experienced this’) to 4 (‘I experienced this very often’) as to how often the described stressful situations were experienced during the past three months. Based on nine subscales it assesses ‘work overload’, ‘social overload’, ‘excessive demands from work’, ‘lack of social recognition’, ‘work discontent’, ‘social tension’, ‘pressure to perform, ‘social isolation’ and ‘chronic worrying’. The measure presents good to excellent results in terms of internal consistency with Cronbach’s α ranging from .84 to .91. A nine-factor solution of a principal component analysis confirms a good construct validity and correlations between the TICS and other stress questionnaires show plausible relationships [50].

#### Co-primary outcome measure

*Brief COPE* [56]. The Brief COPE includes 28 items which measure 14 conceptually differentiable coping reactions. Each scale is measured by two items and comprises effective and ineffective coping strategies such as ‘self-distraction’, ‘active coping’, ‘denial’, ‘substance use’, ‘use of emotional support’, ‘use of instrumental support’, ‘behavioral disengagement’, venting’, positive reframing’, ‘planning’, ‘humor’, ‘acceptance’, ‘religion’ and ‘self-blame’. The participants are asked to rate on a Likert-type scale ranging from 1 (‘not at all’) to 4 (‘very much’) how much the statements resemble the person’s thoughts and actions in demanding or difficult situations in the past. Internal consistency reliabilities were found to be poor to good with a range between .50 and .90 (Cronbach’s α). An exploratory factor analysis provides a nine-factor solution which was similar to results reported for the full inventory [56]. Information about the convergent and discriminant validity is given for the previously published full inventory [57]. Correlations between functional coping strategies and personality qualities regarded as beneficial are reported. Furthermore, the COPE scales were unrelated to a measure which is different to the coping styles assessed in the COPE inventory. A German version of the Brief COPE is available and has been validated [58]. Due to a lack of internal consistency and item variance, the authors of the German translation recommend the selection of 11 subscales which are subsumed under four factors of coping. This solution presents acceptable to good internal consistency with Cronbach’s α ranging from .61 up to .81 [58].

### Secondary outcome measure

*Brief Symptom Inventory (BSI)* [59]. The BSI is a 53-item measure that focuses on impairment due to somatic and psychological symptoms. Based on nine subscales it comprises ‘Obsessive-Compulsive’, ‘Paranoid Ideation’, ‘Hostility’, ‘Somatization’, ‘Depression’, ‘Interpersonal Sensitivity’, ‘Anxiety’, ‘Psychoticism’ and ‘Phobic Anxiety’. On a Likert-type scale ranging from 0 (‘not at all’) to 4 (‘extremely’) the current distress is to be indicated. Reliability estimates for the German version were found to be good in a community sample with Cronbach’s α ranging from .70 to .88. Correlations between the BSI and other instruments show plausible relationships [60].

### Additional measures

*Response Style Questionnaire (RSQ)* [61]*.* In its short version, the RSQ is a 23-item questionnaire of cognitive and behavioral coping styles in response to dysphoric mood. It comprises the three scales ‘symptom-focused rumination’, ‘self-focused rumination’ and ‘distraction’ for which participants are asked to indicate their normal behavior when feeling sad or depressed on a Likert-type scale ranging from 1 (‘almost never’) to 4 (‘almost always’). Psychometric properties referring to the German short version including Cronbach’s α ranging from .75 and .88 were found to be acceptable for a depressed inpatient sample and a community sample. A principle component analysis confirmed the subscales with a three-factor solution. Moreover, convergent and discriminant validity have been confirmed by plausible associations with related and unrelated cognitive constructs [62].

*Skala Impulsives-Verhalten-8 (I-8)* [63]. The I-8 is a German questionnaire that measures impulsive behavior depending on four subscales: ‘immediacy’, ‘purpose’, ‘persistence’ and ‘risk-taking’. These are assessed with two items on a Likert-type scale ranging from 1 (‘doesn’t apply at all’) to 5 (‘applies completely’) referring to how much the statements apply to the participants behavior. Reliability estimates were found to be acceptable to excellent by using McDonald’s omega coefficient ranging from .65 to .92. Due to a confirmatory factor analysis the four factors could be validated. Verification of the construct validity presented good results in terms of plausible associations with related and unrelated cognitive constructs [63].

*Frost Multidimensional Perfectionism Scale (FMPS)* [64]. The FMPS measures different dimensions of perfectionism. According to a differentiated analysis of publications using the FMPS, the author of the German translation recommends a subsumption of the original six subscales into ‘Concerns over Mistakes and Doubts’, ‘Parental Expectations and Criticism’, ‘Personal Standards’ and ‘Organization’ [65]. It consists of 35 items which participants are asked to answer on a Likert-type scale ranging from 1 (‘strongly disagree) to 5 (‘strongly agree’). In the present study only, the subscales ‘Concern over Mistakes and Doubts’ and ‘Personal Standards’ will be applied. Concerning the two selected subscales, this measure presents good results in terms of internal consistency with Cronbach’s α ranging from .78 to .88. Based on the confirmation of the four-factor solution the factorial validity is assessed to be good [65]. In terms of construct validity the new subscales show the same significant relationships with other measures as the original scales [65].

*Freiburg Mindfulness Inventory (FMI)* [66]. The FMI is a German questionnaire that assesses the various attributes of mindfulness. In its short version it comprises 14 items which the participants answer on a Likert-type scale ranging from 1 (‘almost never’) to 4 (‘almost always’) concerning the frequency of reported experience during the past four weeks. Compared to the original instrument, the short form appeared to be easier to answer for subjects without previous meditation experience [67]. The measure presents good results in terms of internal consistency with Cronbach’s α = .86. A one-factor solution of a principal component analysis and correlations between the FMI and other relevant constructs like self-awareness, meditation experience and dissociation confirm a good construct validity [67].

*Short Scale for Measuring General Self-efficacy Beliefs (ASKU)* [68]. The ASKU is a German three-item questionnaire to assess general self-efficacy expectations. Appraisal of one’s own competencies of planning and executing actions in a successful way is given on a Likert-type scale ranging from 1 (‘doesn’t apply at all’) to 5 (‘applies completely’). Data about good internal consistency range from .81 to .86 (McDonald’s ω). Due to a confirmatory factor analysis, the tested model of a one-factor solution could be validated. Verification of the construct validity presented good results in terms of correlations with other measures of self-efficacy expectations and related constructs [68].

*Satisfaction with Life Scale (SWLS)* [69]. The SWLS is a 5-item assessment of life satisfaction. On a Likert-type scale ranging from 1 (‘strongly agree’) to 7 (‘strongly disagree’), respondents indicate the extent to which they agree with each statement. The German version of the measure has good psychometric properties. Reliability estimates in a general population sample were found to be excellent in terms of Cronbach’s α = .92. Evidence of convergent validity is given by plausible relationships between the SWLS and measures of depressiveness and social support [70].

*Skala Internale-Externale-Kontrollüberzeugung (IE-4)* [71]. The IE-4 is a German questionnaire for the assessment of locus of control and comprises the two subscales ‘internal locus of control’ and ‘external locus of control’. Each subscale consists of two items for which the respondents are asked to indicate on a Likert-type scale ranging from 1 (‘doesn’t apply at all’) to 5 (‘applies completely’) how much the statements apply to their own conviction. The measure presents poor to good results in terms of internal consistency with McDonald’s omega coefficient ranging from .53 to .71 in a general population sample. Due to a confirmatory factor analysis, the two factors could be validated. Positive correlations between the subscale ‘internal locus of control’ and general self-efficacy beliefs or optimism confirm a good construct validity. This statistical relationship is exactly reverse concerning the subscale ‘external locus of control’. An additional evidence of convergent validity shows the high association between the IE-4 and an alternative measure of the same construct [71].

*Rosenberg’s Self-Esteem Scale (RSS)* [72]: The RSS is a 10-item questionnaire that assesses global self-esteem. It has been translated into the German language [73] and partially revised by excluding one item that was determined to be psychometrically weak [74]. On a Likert-type scale ranging from 0 (‘strongly agree’) to 3 (‘strongly disagree’), respondents indicate the extent to which they agree with each statement. The evaluation of the revised version presents good results in terms of internal consistency with Cronbach’s ranging from .84 to .85. A one-factor solution of a principal component analysis confirms a good construct validity [74]. Information about the convergent validity of the unrevised version is given by correlations between the RSS and measures of self-efficacy expectations and optimism [73].

### Statistical methods

Descriptive statistics on study population will be calculated for each group at baseline. Means and standard deviations on primary, co-primary, secondary outcome and additional measures will be presented at baseline, post intervention and at the two follow-up time points for each group. A two-folded approach according to Tabachnik and Fidell [75] is used to address missing data. Initially, a Completer-Analysis with a sample of complete data-sets of each person is evaluated. Secondly, an Intent-to-Treat-Analysis with a Last-Observation-Carried-Forward-Method will be applied to check for differences and possible drop-out-effects. The null hypothesis will be rejected at the cut-off of 5% (α-level), therefore a *P* value ≤ .05 will be applied. To evaluate all group x time interactions in one model, we will use an explicatory MANOVA with primary, co-primary and secondary outcome. We expect differential time x group effects on secondary outcome at the one year/five year follow-up after post-intervention assessment. Therefore, this preliminary analysis will be called ‘explicatory’. For confirmatory analysis following the assumption that primary and co-primary outcome are separate hypothesis, both hypotheses will be tested in separate repeated-measures ANOVA’s with the factorial structure group (MediMind, Autogenic Training and control group) x time. The hypothesis will be evaluated through testing interaction effects. Orthogonally constructed comparisons are then used to check for pairwise differences. If needed, Holm-Bonferroni corrected pairwise comparisons will be used [76]. Additionally post-hoc sub-group comparisons (sex, semester, cohort) will be conducted to analyze data sets furthermore.

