**Discussion:**

Potential limitations of this study are voluntary participation and the risk of attrition, especially concerning participants that are allocated to the control group. Strengths are the study design, namely random allocation, follow-up assessment, the use of control groups and inclusion of participants at different stages of medical training with the possibility of differential analysis.

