### Participants and recruitment

Participants are medical students in the second and eighth semester. In addition to students of human medicine in the preclinical cohort, dental students will be included. Their curriculum and learning environment is nearly analogous to medical students in the preclinical semesters. Students that fit these eligibility criteria and study at the Johannes Gutenberg-University Mainz form a cohort of approximately 420 students in each academic term (second semester: 50 dental and 200 medical students; eighth semester: 170 medical students). It is expected to recruit a minimum of 30% of the possible participants according to literature [17] each semester resulting in an initial sample size of 126 participants. Over the course of time between baseline and five-year follow-up we expect a maximum dropout rate of 50% leading to a final sample size of 189 participants with participants of 3 semesters. The optimal sample size was calculated through analyzing and integrating related publications [16,17,21] via effect sizes (F-values respective η-square-values, Cohen’s d and Λ for multivariate approaches) with G*Power [47]. A synopsis of needed sample sizes for the different articles and different outcome measures within the articles was constructed and evaluated. This resulted in an approximate value of the minimum total sample size of 126 participants at five-year follow-up for valid analysis of secondary outcome.

Students are informed about the project via e-mail, and the Department of Medicine student body shares information on their social network. Additionally, our team introduces the study design and the opportunity for participation at lectures. At that time, we hand out written information and informed consent. Students who return the signed informed consent are introduced to the baseline assessment. They have the choice of either filling out the questionnaire as a paper-and-pencil version or completing an online version. In addition to the signed informed consent, the completion of the baseline assessment is a requirement of becoming assigned to the study groups.

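### A completer analysis checked only by last observation carried forward is a weak safeguard for the year-five comparison when up to half the sample may be lost

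*Protocol article*

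**What the plan says.** The section Statistical methods describes a two-part approach to missing data. The first part is: "Initially, a Completer-Analysis with a sample of complete data-sets of each person is evaluated". The second is: "Secondly, an Intent-to-Treat-Analysis with a Last-Observation-Carried-Forward-Method will be applied to check for differences and possible drop-out-effects". No other missing-data method is named. The confirmatory tests are repeated-measures ANOVAs of group by time.

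Participants and recruitment gives the expected loss: "we expect a maximum dropout rate of 50% leading to a final sample size of 189 participants with participants of 3 semesters". It also sets a "minimum total sample size of 126 participants at five-year follow-up for valid analysis of secondary outcome".

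Three other places bear on the point:
- Assessment time points puts the post-intervention wave three weeks after the last session, and the last wave five years after that.
- Primary and secondary aim expects the effect on psychological morbidity to show only at follow-up.
- The Abstract lists as a limitation "the risk of attrition, especially concerning participants that are allocated to the control group". The main Discussion expects control-group response to be difficult already at post-intervention, and says stress may differ between the second and eighth semesters.

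**The concern.** Both methods are fixed in the text, so this is not detail left to an analysis plan that is not shown.

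The completer analysis discards scores that were observed. It estimates the randomised comparison without bias only if leaving is unrelated to outcome. LOCF keeps everyone, but assumes that nothing changes between the last score and year five, and it treats the filled-in value as an observation. The protocol itself describes a long gap, heavy loss, a morbidity effect that develops over time, and attrition concentrated in one arm. These are the conditions in which LOCF does badly.

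At stake is the year-five group comparison and the planned use of LOCF to judge whether dropout has distorted the results.

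**Working it through.** **Reproducing the plan's figure.** 0.30 × 420 = 126 per semester; 3 × 126 = 378; 378 × (1 − 0.50) = 189, as stated. At the maximum dropout, 189 of 378 year-five values would be carried forward. If recruitment only just secures 126 at year five, 126 / 0.50 = 252 are randomised and 126 values are carried.

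**Which score is carried.** Baseline completion is a condition of allocation, so someone lost before the post wave carries baseline. Someone lost between post and one year carries the three-week score, and later losses carry the one-year score. The documents do not give the split. Effect sizes are not given either, so the values below are assumptions in SD units.

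**LOCF with equal dropout d = 0.50.** Expected year-five contrast = (1 − d)·e5 + d·(share at post·e_post + share at one year·e_1y). Those last seen at baseline contribute 0.

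| Effect at post / 1 y / 5 y | Dropouts last seen | LOCF result | Error |
|---|---|---|---|
| 0.50 / 0.25 / 0 | all at post | 0.25 | +0.25 |
| 0.50 / 0.25 / 0 | half post, half 1 y | 0.1875 | +0.1875 |
| 0.50 / 0.25 / 0 | all at 1 y | 0.125 | +0.125 |
| 0.50 / 0.25 / 0 | 30/40/30% baseline/post/1 y | 0.5 × (0.4 × 0.50 + 0.3 × 0.25) = 0.1375 | +0.1375 |
| 0 / 0.25 / 0.50 | all at post | 0.25 | −0.25 |
| 0 / 0.25 / 0.50 | all at 1 y | 0.375 | −0.125 |
| 0.50 / 0.50 / 0.50 | nobody at baseline | 0.50 | 0 |
| 0.50 / 0.50 / 0.50 | one third each | 0.417 | −0.083 |

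**LOCF with unequal dropout and no effect.** Assume 45% dropout in each training arm and 70% in control. With 2:2:1 allocation this is 0.8 × 0.45 + 0.2 × 0.70 = 0.50 overall. Assume stress rises by 0.2 SD at one year and 0.5 SD at five years in every arm, with the 30/40/30% split.
- MediMind: 0.55 × 0.5 + 0.45 × 0.3 × 0.2 = 0.302.
- Control: 0.30 × 0.5 + 0.70 × 0.3 × 0.2 = 0.192.
- Difference: 0.110 SD against MediMind, created by the method alone.

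**Rejection rates.** Simulation of MediMind against control, correlation 0.5 between waves, t-test on carried-forward change at year five, arms of 101/50 (252 randomised) and 151/76 (378 randomised).
- Faded effect (the 0.1375 row): 13% and 17 to 18%.
- Unequal dropout with no effect: 10% and 12 to 13%.
- Completers in the same scenarios: bias no more than 0.006 SD, rejection about 5%. Dropout in these scenarios does not depend on outcome within an arm.

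**Outcome-dependent dropout.** A second simulation lets dropout rise with the last observed score, to about 45–53% in MediMind and 71–73% in control. Negative values favour MediMind.

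| Case | Truth | Completers | LOCF | Likelihood-type estimate (missing at random) |
|---|---|---|---|---|
| Fading effect | 0 | +0.12 | −0.18 | 0.00 |
| Emerging effect | −0.50 | −0.40 | −0.31 | −0.50 |

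**Precision of completers at one year.** This applies only if complete data means all four waves. Assume retention of 85/70/50% and 252 randomised. One-year responders number 70.6 and 35.3, so SE = √(1/70.6 + 1/35.3) = 0.206 SD. Completers number 50.4 and 25.2, so SE = √(1/50.4 + 1/25.2) = 0.244 SD. The variance ratio is 0.70 / 0.50 = 1.40.

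**The case against.** The strongest reply is that LOCF is only the check. The analysis run first is the completer analysis, and in the scenarios behind the 10 to 18% it is essentially unbiased with correct error rates. This stands: those figures indict the check and not the first analysis. Completer bias appears only when dropout is made to depend on the score, and the documents do not describe that mechanism.

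It also stands that the simulated test is a two-arm comparison at year five, not the planned three-group interaction test. With a real post-intervention effect the interaction null is false, so the rejection rate concerns the year-five contrast alone. Decay, drift, correlation and dropout splits are all assumed. The article also offers every responding control participant a voucher, which may narrow the difference in dropout.

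A reader might go further and infer any of the following, which the documents do not support:
- **That half the year-five values would be three-week scores.** This holds only for people lost between post and one year, and 50% is stated as a maximum.
- **That the two analyses fail in opposite directions, or that their agreement must mislead.** Either can be produced by choosing a dropout model; neither follows from the text.
- **That completers must have all four waves.** This is a natural reading, but completers defined wave by wave are not excluded. The 40% variance penalty depends on it.

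None of this makes LOCF a sound check, or justifies setting observed data aside in the leading analysis.

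**Conclusion.** The concern holds in conditional form. The plan leads with an analysis that leaves the randomised set, and its only intention-to-treat check relies on no change after the last observation. The protocol's own expectations run against that assumption: the morbidity effect is to emerge at follow-up, and attrition is to be worst in control.

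The LOCF error is 0.11 SD (unequal dropout with drift) and 0.14 SD (faded effect) in the two simulated scenarios. It is 0.125 to 0.25 SD for fading or emerging effects at 50% dropout when nobody is last seen at baseline. Its sign can go either way. It is zero if the effect is constant, dropout is balanced and nobody is last seen at baseline, so bias is not certain. For completers, the demonstrated cost is lost precision on the four-wave reading; bias is possible but rests on an assumed dropout mechanism.

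**What to change.** Make the main analysis a likelihood-based mixed model for repeated measures on all randomised participants: group by time, unstructured covariance, baseline in the model, every observed wave used. Take the year-five contrasts from that model. Drop LOCF. Because the mixed model relies on data missing at random, add two sensitivity analyses: multiple imputation with the additional questionnaires as auxiliary variables, and a delta-shift analysis over a stated range that includes a separate shift for control-group dropouts. Keep the completer analysis as secondary, and say whether complete means all four waves.

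The cost is revised wording and some programming; the statistical package already named has a mixed-model procedure. No further data or participants are needed. Year-five intervals will be wider than under LOCF, because they reflect the information actually observed.
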